#### Indirect calorimetry

Fasted resting metabolic rate was measured using indirect calorimetry (BodyGem; Microlife Medical Home Solutions, Inc.). Before assessment, participants rested in the supine position for ≥20 min in a quiet and dimly lit room. During the measurement, participants sat quietly with their feet flat on the floor. Participants were asked to breathe into a disposable mouthpiece connected to the indirect calorimeter until steady-state oxygen consumption was reached (5–10 min). The indirect calorimeter measures oxygen consumption, which is converted to calories using the Weir equation and a constant respiratory quotient value of 0.85 [10].

#### Resting blood pressure

After ≥5 min of seated rest, blood pressure was measured with an automated cuff (Omron HEM-907XL; Omron Healthcare, Inc.). Three measurements were taken, separated by ≥1 min, and averaged to calculate resting blood pressure.

#### Hemoglobin mass and blood volume

Hemoglobin mass (Hbmass) was determined in a subset of participants (*n* = 230) using the automated carbon monoxide (CO)-rebreathing method (Detalo Health). The amount of time to complete measurements (∼10–15 min/participant) and the availability of equipment and supplies limited the number of participants able to complete this measure. The method is based on the dilution principle, where a small volume of tracer (CO) is administered, and the subsequent concentration of carboxyhemoglobin (COHb) in the blood can be used to calculate Hbmass. Red blood cell volume, plasma volume, and total blood volume can then be calculated from Hbmass. CO was administered to participants in combination with 100% O_2_. The gas mixture was then rebreathed within a closed system for 4 min. Before and 6 min after CO-rebreathing, arterialized capillary blood was collected from a fingertip to assess changes in COHb (%) using a blood gas analyzer (OSM3; Radiometer). Consistent with previous methods [11], each blood sample was measured in triplicate. If the results differed by >0.1%, 2 additional samples were collected (for a total of 5).

#### Physical activity and sleep

Physical activity and sleep data were collected by actigraphy (Actigraph GT3X+; ActiGraph) in a self-selected subset of participants (*n* = 174). Actigraphy assessments were optional and based on device availability. The actigraph was worn on the nondominant wrist for ≥5 d. Acceleration data were recorded every 15 s and computed using the Freedson Adult thresholds to estimate metabolic equivalents and step counts and identify activity type, such as sedentary, light, moderate, vigorous, and very vigorous activity [12]. Adherence to the activity monitor was obtained through the “wear time” function in ActiLife software (ActiGraph). Data from the first and last day of wear were not included in the analysis, and 3-d averages were computed for participants with ≥3 d of >10 h of awake time data.

For sleep analyses, raw actigraphy data were saved as 60-s epoch files and imported into ActiLife using the batch sleep processing feature. The Cole–Kripke sleep algorithm [13] and the Tudor-Locke algorithm [14] were applied using default settings to detect sleep periods. Averages for total sleep time, sleep efficiency, and wake after sleep onset were calculated from 3 d of wear time (i.e., days 2–4). Participants were asked to record information related to their sleep habits on the days they wore the accelerometer.

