## Trial aim

The aim of MHANES is to provide comprehensive information on nutritional, biochemical, and medical status and lifestyle behaviors of active-duty Army Soldiers by assessing dietary intake, cardiometabolic health, body composition, biomarkers of nutritional status and health, mental well-being, sleep, physical activity, injury prevalence, genetics, gut microbiome composition, and physical performance in a large representative sample of Army Soldiers.

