### Study population and trial design

In this cross-sectional study, data were collected from August 2024 to February 2026 in active-duty Army Soldiers (*n* = 648) from the following 5 geographically dispersed Army installations in the United States: Fort Polk, Louisiana; Fort Campbell, Kentucky; Joint Base Lewis-McChord, Washington; Fort Carson, Colorado; Fort Stewart, Georgia (Table 1). These Army installations represent a convenience sample because selection was based on the availability of a letter of support from the Commanding General at each installation. Marketing efforts at each installation were as broad as possible to ensure adequate sampling across demographic subgroups of sex, race/ethnicity, and grade/rank and, ultimately, to recruit a representative sample of active-duty Army Soldiers. In addition, we oversampled females and certain race/ethnicity groups to ensure that these groups are adequately powered for analyses (Table 2). For example, females were oversampled because they are a smaller proportion of the Army population and are at greater risk of several nutritional deficiencies including iron and iodine [4,5].

**TABLE 1 tbl1:** Data collection location, dates, and enrollment for the Military Health and Nutrition Examination Study (MHANES) population

Location	Date	Enrollment
Fort Polk, LA	August to September 2024	126
	January to February 2026	38
Fort Campbell, KY	September to October 2024	134
Joint Base Lewis-McChord, WA	January to February 2025	137
Fort Carson, CO	March to April 2025	123
Fort Stewart, GA	July to August 2025	90

**TABLE 2 tbl2:** Oversampling plan for the Military Health and Nutrition Examination Study (MHANES) population

	Percentage of the Army population^1^	Percentage of the MHANES population^2^
Sex		
Female	16	32
Male	84	68
Race/ethnicity		
American Indian or Alaskan	2	4
Native/other/unknown		
Asian or Pacific Islander	7	14
Non-Hispanic Black	21	21
Hispanic	17	17
Non-Hispanic White	53	44
Rank		
Enlisted	82	82
Officer	18	18

1 Based on demographics from 2021.

2 Target demographics for MHANES.

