Post-stratification survey weights were applied to align the analytic sample with the demographic composition of the active-duty Army population based on sex, race/ethnicity, and rank. Although these weights do not explicitly account for site-based recruitment, they help mitigate potential bias to the extent that differences across installations are reflected in these characteristics. In addition, active-duty Soldiers routinely relocate between installations approximately every 3 to 4 y, resulting in broadly similar demographic distributions across sites. Steps to minimize sampling bias included geographic dispersion of installations, broad recruitment strategies at each site, and balanced enrollment targets across installations (∼100–150 participants at each site).

Interested Soldiers attended an in-person briefing to learn about the study and, if still interested in participating, signed the informed consent before any data collection. The study inclusion and exclusion criteria are shown in Table 3. After signing the informed consent, volunteers are asked to complete a screening questionnaire to obtain demographic information (i.e., sex, age, race/ethnicity, rank/grade, area of assignment, military occupational specialty, and duration at current duty station). Volunteers were then given instructions (i.e., no alcohol for 48 h, no exercise or caffeine for 12 h, no food or beverages except water for 10 h, and no tobacco or nicotine products in the morning before the visit) and scheduled for 1 in-person visit (∼4 h) where outcome measures were assessed (see below). A stool sample kit was provided to volunteers so they could collect the sample at home and bring it to the study visit. Volunteers were also provided with a bag to carry their dietary supplements and medications to the study visit. A subset of volunteers received an actigraph watch to monitor sleep and physical activity to wear until their in-person visit (∼4–7 d after the briefing visit).

**TABLE 3 tbl3:** Inclusion and exclusion criteria for the Military Health and Nutrition Examination Study

Inclusion criteria	Exclusion criteria

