#### Body composition measured using dual-energy X-ray absorptiometry

At installation(s) with an accessible dual-energy X-ray absorptiometry (DXA) machine (i.e., Fort Stewart), all participants (*n* = 90) were asked to undergo a DXA scan. Body composition (total body weight, fat-free mass, fat mass, and bone mass) was determined after an overnight fast (Lunar Prodigy; General Electric). A pregnancy test was administered to all females before the DXA scan to confirm that they were not pregnant.

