#### Doubly labeled water method

A subset of participants (*n* = 106) was dosed with doubly labeled water to assess total daily energy expenditure (TDEE). TDEE assessment, an optional study measure, was collected in as many participants as feasible within logistical and budgetary constraints. Before dosing, volunteers provided a urine sample that was used to measure background isotope enrichment. The participant then consumed 1.5 g/kg body weight of a mixture of 1.425 g 10% H_2_^18^O per kg body weight and 0.075 g 99.8% ^2^H_2_O per kg body weight (Sigma-Aldrich). The container was rinsed with ∼50 mL bottled water for the participant to then consume. Urine was collected at 4.5 h and 7 d after dosing. Isotopic elimination rates were calculated using regression and the equation developed by Speakman et al. [15] to assess the rate of carbon dioxide (CO_2_) production. Energy expenditure was calculated by multiplying the rate of CO_2_ production by an assumed food quotient of the diet of 0.86.

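### Actigraphy, doubly labeled water, hemoglobin mass and DXA results come from selected subsets and cannot be presented as Army-representative with weights built only on sex, race/ethnicity and rank

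*Protocol article*

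**What the plan says.** The *Trial aim* section lists body composition, sleep and physical activity among the things assessed, and ends the list with "gut microbiome composition, and physical performance in a large representative sample of Army Soldiers". Enrollment is given under *Study population and trial design*: "data were collected from August 2024 to February 2026 in active-duty Army Soldiers (*n* = 648".

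Four device measures were taken in only part of that sample:

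- **Actigraphy** (*Physical activity and sleep*): collected "in a self-selected subset of participants (*n* = 174", with the explanation "Actigraphy assessments were optional and based on device availability".
- **Doubly labeled water** (*Doubly labeled water method*): "A subset of participants (*n* = 106) was dosed with doubly labeled water"; "TDEE assessment, an optional study measure, was collected in as many participants as feasible within logistical and budgetary constraints".
- **Hemoglobin mass** (*Hemoglobin mass and blood volume*): 230 participants, limited by measurement time, equipment and supplies.
- **DXA** (*Body composition measured using dual-energy X-ray absorptiometry*): "At installation(s) with an accessible dual-energy X-ray absorptiometry (DXA) machine (i.e., Fort Stewart". All 90 participants there were asked to have a scan.

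On weighting, *Study population and trial design* says "Post-stratification survey weights were applied to align the analytic sample with the demographic composition of the active-duty Army population", and names sex, race/ethnicity and rank as the weighting variables. It adds that the weights do not explicitly cover recruitment by site. *Statistical analyses* plans means, standard errors and distributions for every variable in the whole sample, with survey weights applied, and makes no exception for the four subset measures.

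**The concern.** Post-stratification makes the weighted sample match the Army on the three weighting variables. It corrects selection only as far as participants and non-participants of the same sex, race/ethnicity and rank are alike on the measured trait. There is no reason to assume this for an activity monitor worn by choice, since willingness to wear one may well go with sleep and training habits. For DXA the difficulty is coverage: all scans come from Fort Stewart in July to August 2025 (Table 1), and weighting on demographics cannot supply the other installations.

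The article says its findings are meant to guide screening, intervention and policy. A weighted mean of actigraphic sleep, energy expenditure or DXA fat, computed as the plan describes and read alongside the aim, would be taken as an Army value when it describes volunteers or a single post.

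**Working it through.** **Denominator.** Table 1 enrollments are 126 + 38 + 134 + 137 + 123 + 90 = 648, which matches the stated total.

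**Subset shares and precision.** Share = n/648. The 95% half-width for a proportion is 1.96 × √(p(1 − p)/n), shown at an assumed p = 0.3. The last column multiplies the variance by a design effect of 1.19. That figure comes from the Table 2 Army and target percentages, as Σ(Army²/target) for sex (1.118) times the same sum for race/ethnicity (1.063), treating the two margins as independent.

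| Measure | n | Share | Half-width, unweighted | Half-width, weighted |
|---|---|---|---|---|
| Full sample | 648 | 100% | 3.5 points | 3.8 points |
| Hemoglobin mass | 230 | 35.5% | 5.9 | 6.5 |
| Actigraphy | 174 | 26.9% | 6.8 | 7.4 |
| Doubly labeled water | 106 | 16.4% | 8.7 | 9.5 |
| DXA | 90 | 13.9% | 9.5 | 10.3 |

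At the 32% female target the subsets would hold about 0.32 × 90 = 29 women for DXA, 0.32 × 106 = 34 for doubly labeled water and 0.32 × 174 = 56 for actigraphy. The achieved composition of the subsets is not given.

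**Bias left after demographic weighting, for a mean.** Let d be the difference between participants and non-participants within strata of sex, race/ethnicity and rank. Take d and the participation rate to be the same in every stratum. Relative to the 648 enrolled, the bias of the weighted subset mean is then (1 − n/648) × d. For actigraphy, 1 − 174/648 = 0.731:

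- d = 10 min gives 7.3 min
- d = 20 min gives 14.6 min
- d = 30 min gives 21.9 min

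The unweighted sampling half-width at an assumed SD of 60 min is 1.96 × 60/√174 = 8.9 min. Neither the differences nor the SD is in the documents.

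**The same, for a proportion.** Let p be the true proportion with a condition, q the participation rate among those with it and m the rate among those without. Require pq + (1 − p)m = 174/648 and [q/(1 − q)]/[m/(1 − m)] = OR. The observed proportion is pq/(174/648). With an assumed opt-in odds ratio of 0.5 to 2, unrelated to the weighting variables:

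- a true 30% is observed as 20.2% to 41.2%
- a true 50% is observed as 37.5% to 62.5%

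At p = 0.3 the shift is about 10 to 11 points, against a half-width of 6.8 points.

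**Measures in the same domains with no stated subset restriction.** Body composition: bioelectrical impedance, 2D/3D imaging and tape circumferences. Sleep: PSQI and the sleep-habits scale of the eating-behaviors survey. Physical activity: the Lifestyle and Health Questionnaire and the activity scale of the same survey.

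**The case against.** The article is open about all of this. It gives each subset's size and the reason for it, calls the installations a convenience sample and states the limit of the weights. The statistical section is a short summary, and a condensed article may leave subset weights to a fuller plan. That stands, so the absence of a subset-weighting method is not the point. What remains is that the article does fix the weighting variables, does plan weighted estimates for every variable, and does not limit the aim's representative wording for these measures.

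A reader might infer three stronger things that the documents do not support:

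- **That the sleep, activity and body composition objectives go unanswered for the Army.** The aim names domains, not devices, and each domain has measures with no stated subset restriction.
- **That the aim promises all four device measures.** It names neither energy expenditure nor hemoglobin mass, and it does not mention DXA.
- **That all four subsets are self-selected.** Only actigraphy is described so. Doubly labeled water was optional, hemoglobin mass was capacity-limited, and DXA was offered to everyone at its site.

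It is also fair to say that the bias figures are assumed. At a 10 min difference the bias (7.3 min) is smaller than the half-width (8.9 min), and only the difference remaining within demographic strata counts.

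A participation model has its own limit. Watches were issued at the briefing and worn until the visit, and the questionnaires were completed at the visit. PSQI and self-reported activity therefore come after the choice to participate, and wearing the device may have affected the answers.

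**Conclusion.** The concern holds for the device-measured results, not for the domains as a whole. Under the stated plan, actigraphic sleep and activity, total energy expenditure, hemoglobin mass and DXA body composition cannot be presented as Army-representative. They rest on 13.9% to 35.5% of those enrolled, reached by opt-in, capacity limits or a single site, and the weights adjust for three demographic variables only.

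This conclusion needs no assumed number. The size of the bias is unknown from the documents. The 7 to 22 min of sleep and the 20% to 41% around a true 30% are illustrations under assumed differences that persist within demographic strata. They show that bias could match or exceed sampling error, not that it does. The full-sample measures still share the study's convenience choice of installations, which is a separate limitation.

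**What to change.** 1. Limit the representative wording in the aim and conclusions to the full-sample measures. Name PSQI, questionnaire activity, impedance and circumferences as the basis for Army-level statements on sleep, physical activity and body composition.
2. Report actigraphy, doubly labeled water and hemoglobin mass as subset findings. Tabulate participants against non-participants for each, and re-rake the weights within each subset to the Army margins. Add a participation-propensity adjustment as a sensitivity analysis, relying mainly on variables fixed before participation: sex, age, race/ethnicity, rank, occupational specialty, and site where the measure was offered at several sites. Treat PSQI and self-reported activity with caution as predictors, because they were collected after the watch was worn.
3. Use the Fort Stewart DXA data to validate or calibrate impedance and imaging, not for Army-level estimates.

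The cost is analysis-plan wording, comparison tables and one sensitivity model for each of the three subsets in item 2, all on data already collected. Subset intervals become wider and the stated aim slightly narrower. The adjustment cannot remove selection on traits that were not measured, so the subset label should stay whatever the sensitivity analysis shows.

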#### Doubly labeled water method

A subset of participants (*n* = 106) was dosed with doubly labeled water to assess total daily energy expenditure (TDEE). TDEE assessment, an optional study measure, was collected in as many participants as feasible within logistical and budgetary constraints. Before dosing, volunteers provided a urine sample that was used to measure background isotope enrichment. The participant then consumed 1.5 g/kg body weight of a mixture of 1.425 g 10% H_2_^18^O per kg body weight and 0.075 g 99.8% ^2^H_2_O per kg body weight (Sigma-Aldrich). The container was rinsed with ∼50 mL bottled water for the participant to then consume. Urine was collected at 4.5 h and 7 d after dosing. Isotopic elimination rates were calculated using regression and the equation developed by Speakman et al. [15] to assess the rate of carbon dioxide (CO_2_) production. Energy expenditure was calculated by multiplying the rate of CO_2_ production by an assumed food quotient of the diet of 0.86.

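### The stated rule for doubly labeled water energy expenditure, CO2 production times a food quotient of 0.86, yields a gas rate and not an energy

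*Protocol article*

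**What the plan says.** Under Doubly labeled water method, the protocol article reports: "A subset of participants (*n* = 106) was dosed with doubly labeled water". The purpose given is TDEE, and the measure is described as optional. Isotope elimination rates go into a cited equation "to assess the rate of carbon dioxide (CO_2_) production". The last step, from gas to energy, is then stated as an explicit operation: "Energy expenditure was calculated by multiplying the rate of CO_2_ production by an assumed food quotient of the diet of 0.86". The section gives no unit for CO2 production or TDEE, no energy value per unit of CO2, and no energy equation.

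Under Indirect calorimetry, the same article describes the comparable step for resting metabolic rate differently. There, measured oxygen consumption is "converted to calories using the Weir equation and a constant respiratory quotient value of 0.85". The doubly labeled water section does not refer to that step.

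**The concern.** The only number offered for turning CO2 into energy is "an assumed food quotient of the diet of 0.86". A food quotient is a ratio of two gas amounts, and multiplying by a ratio cannot turn gas into energy. A missing constant is not the whole difficulty, because the operation also runs the wrong way. The quotient links CO2 to O2 by division, and the energy released per litre of CO2 falls as the quotient rises, whereas the stated product rises with it.

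TDEE is the only stated purpose of the doubly labeled water measurement. A reader who follows the sentence would obtain a wrong value for each of the 106 participants. The article foresees release of data, codebook and code on request and controlled access for external investigators, so people outside the team may rely on this description.

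**Working it through.** The article reports no TDEE value and no energy constant, so there is no figure of its own to reproduce. The check is one of dimensions, then direction, then scale.

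**Inputs from the article**
- Stated rule: energy expenditure = rCO2 × 0.86, where rCO2 is the CO2 production rate (Doubly labeled water method).
- Food quotient FQ = 0.86; subset n = 106 (same section).
- Weir equation named, with a respiratory quotient of 0.85, for a different measurement (Indirect calorimetry).

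**Assumptions not in the article**
- Weir coefficients: 3.941 kcal per L O2 and 1.106 kcal per L CO2.
- 22.4 L per mole of gas; 4.184 kJ per kcal.

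**Step 1, dimensions.** FQ = CO2 produced / O2 consumed, which has no units. With rCO2 in L/d, rCO2 × FQ is in L/d; with rCO2 in mol/d, it is in mol/d. Neither is an energy per day.

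**Step 2, direction.** O2 consumption is rCO2 / FQ. The stated product relative to that is FQ × FQ = 0.86 × 0.86 = 0.74. So even if the product were taken as an O2 rate, it would be 26% too low in any unit system.

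**Step 3, a form that does give energy (illustration).** Putting VO2 = rCO2 / FQ into the Weir equation gives

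TDEE = rCO2 × (1.106 + 3.941/FQ).

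At FQ = 0.86: 3.941/0.86 = 4.583, and 4.583 + 1.106 = 5.689 kcal per L CO2. With rounded coefficients 3.9 and 1.1 it is 5.635.

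| FQ | Multiplier as stated | Weir form, kcal per L CO2 |
|---|---|---|
| 0.80 | 0.80 | 6.03 |
| 0.86 | 0.86 | 5.69 |
| 0.90 | 0.90 | 5.48 |

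The two columns move in opposite directions, so attaching units to the stated rule would not repair it.

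**Step 4, scale for one assumed person.** With rCO2 = 500 L/d, the stated rule returns 500 × 0.86 = 430, still litres of CO2 per day. The Weir form returns 500 × 5.689 = about 2,844 kcal/d.

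**Step 5, why no single error factor can be given.** Energy equivalent divided by 0.86:

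| Units | Energy equivalent per unit of CO2 | Divided by 0.86 |
|---|---|---|
| kcal, L | 5.689 | 6.6 |
| kJ, L | 5.689 × 4.184 = 23.80 | 27.7 |
| kcal, mol | 5.689 × 22.4 = 127.4 | 148 |
| MJ, mol | 127.4 × 4.184 / 1000 = 0.533 | 0.62 |

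**The case against.** The best defence is that the sentence is shorthand. A journal article condenses, and the authors probably meant CO2 production multiplied by the energy equivalent of CO2 at an assumed food quotient of 0.86. Quoting a food quotient has little purpose unless it enters such an equation. That reading is plausible, and it is why the article supports a finding of misdescription only. It does not rescue the text: the sentence states a definite operation that is wrong, rather than leaving detail to another document, and no other section corrects it.

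A reader might infer that TDEE is wrong for all 106 participants. The article does not show this. It reports no TDEE values and no code. Its data-quality section provides for review of implausible values, and figures near 430 for a Soldier's daily expenditure would stand out. That safeguard has limits: if a script multiplied by 0.86 to get O2 and then applied an O2 energy equivalent, a true 3,000 kcal/d would come out at 3,000 × 0.74 = about 2,220, which could pass as plausible.

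A reader might also quote an error factor of 6.6. It holds only for litres, kcal and coefficients that the article does not print, and a quantity that is not an energy has no unit-free error factor.

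Finally, the reach is limited. TDEE is optional, was measured in 106 of 648 participants (16%), and appears neither in the trial aim nor in the sample-size basis nor among the named analyses. This stands and lowers the weight of the point.

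**Conclusion.** The stated formula is wrong. A CO2 rate multiplied by a dimensionless 0.86 is neither an energy nor an O2 rate, so it cannot yield TDEE. This rests only on the definition of a food quotient and on no assumed constant. The 26% shortfall against O2 consumption is likewise free of units.

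The comparison of 5.69 kcal per litre with a multiplier of 0.86 is illustrative. It depends on assumed Weir coefficients, and the article does not say that the Weir equation was the one used for doubly labeled water. The Indirect calorimetry wording serves only as a contrast; it is not a second instance of the problem, and it does not contradict the doubly labeled water section.

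The point affects the doubly labeled water subset alone. It should be corrected, but it becomes a serious defect only if the script proves to have followed the sentence as written.

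**What to change.** Replace the sentence with the energy-equivalent equation actually used for doubly labeled water. State its constants and the units of CO2 production and TDEE, with 0.86 entering as the food quotient. One possible form, if it is the one that was used, is TDEE (kcal/d) = rCO2 (L/d) × (1.106 + 3.941/FQ), FQ = 0.86. Another equation should be reported as such.

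Then compare the calculation script with the corrected sentence. If they agree, nothing else changes. If they do not, recompute the 106 values from the existing CO2 production rates and update any file already shared. The cost is one sentence and a short code check; no new data are needed.
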